**Fig. 1 Fig1:**
[figure not shown]
Timeline of study activities

### Measures

As shown in the Supplementary Table, the primary outcome of the study is PrEP initiation, which we measure by pharmacy fill date (record review) with a signed release of information. The secondary outcome is PrEP adherence by objective measure, which we assess with a urine assay for tenofovir levels (for participants initiating tenofovir-based PrEP) and injection dates for patients initiating injectable cabotegravir for PrEP. Additional health behavior outcomes of interest are shown in the Table, including self-reported PrEP adherence, 6-month PrEP care retention, use of other HIV prevention tools, engagement in the OUD treatment cascade, and new diagnoses of HIV, viral hepatitis, STIs, or pregnancy. We will review the EHR medication list for PrEP and/or MOUD prescriptions after each clinical visit. If patients receive PrEP and/or MOUD prescriptions outside of our respective EHR-covered health systems, the research assistant will obtain prescription fill and refill dates from clinics and pharmacies with a signed release of information and a phone call on each follow-up interview day.

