#### Intervention arm

Participants randomized to the Athena strategy arm will receive the decision aid and integrated PrEP/MOUD via eHealth- a low-demand model designed to reduce social and structural barriers to entry. The research team will schedule an appointment for an eHealth visit and provide instructions on how to access and initiate the visit. Acknowledging high rates of homelessness and IPV-exposure and limited health literacy, we will use teach-back methods to ensure participants can access eHealth safely. At the planned appointment time, the participant will check-in using the dedicated electronic health record (EHR) at each site via mobile app or website. Each EHR provides appointment reminders, clinician interaction, prescription refills, and lab orders and results. The check-in will generate an encounter so that the patient can be “arrived” by the virtual front desk. eHealth will be delivered by the onsite PrEP clinician, who will operate separately from the investigative team to minimize potential bias. Clinicians for this study are both advanced practice providers (APRN or PA) with active licenses to practice medicine in the relevant state (CT or AL), have experience providing PrEP and MOUD, and have experience working with the target population of WICL. The clinicians for this study will not contribute to the evaluation or assessment of outcomes to minimize potential bias. Clinicians are based in a community site and can include community-based PrEP navigators/case managers via videoconferencing if needed, who can help address potential structural barriers (e.g., insurance, copay coverage) to accessing PrEP through eHealth. We selected each of these community sites because both are sites for clinical care and clinical research that serve large populations who are involved with the criminal legal system. Unlike the current requirements for billing reimbursement, eHealth allows patients to be at home (to reduce care burden for WICL) rather than being seen at an established medical site; they may also choose an in-person interaction at the community site. The reason for this flexibility is to ensure that care can be delivered, regardless of technology access limitations, and mechanism of care delivery is one of the things we propose to measure as part of care delivery. For example, if a participant has limited broadband access or limited phone minutes, they may be unable to participate in a telehealth visit and may opt instead to come into our community site and use a study iPad/desktop to meet virtually with the Athena PrEP clinician, or to meet with the Athena PrEP clinician in person.

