
Prior to the visit, the clinician will complete a pre-visit checklist that includes reviewing output from the decision aid and point-of-care (POC) testing in REDCap, reviewing the electronic medical record, and ensuring the telehealth visit is appropriately scheduled. As part of the pre-visit activities, the Athena clinician will review and enter participant-entered and POC baseline assessment data into the EHR, using a preset template with Smart-phrases to facilitate provider communication across health systems. During the encounter, clinicians will discuss the EHR documentation described above with the patient, videoconference (synchronously) with participants and write a note in the EHR, based on a stored template. The clinician will follow standard clinical guidelines for PrEP and discuss patient preference [42]. If clinically indicated and preferred, the clinician will electronically prescribe PrEP to the patient’s choice of pharmacy. The patient will then be responsible for obtaining the medication from the pharmacy.

Based on clinical assessments and need, and following standard clinical guidelines for MOUD [43], clinicians will also offer OUD treatment options that may include: buprenorphine/naloxone, adherence counseling/support for methadone, or coordination with outpatient treatment providers. The specific PrEP and MOUD regimen (doses and/or combination of medications) is not dictated by the protocol and will be instead up to the discretion of the clinician and patient preference. Clinicians are not required by the protocol to prescribe PrEP. PrEP provision is based on patient preference and clinician judgment; it is possible that participants will not be prescribed PrEP or MOUD during the clinical visit. Even if participants are not prescribed PrEP and/or MOUD, they will remain in the study and continue with follow-up study visits.

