#### Enhanced standard of care arm

Decision aid-only participants will receive a printed document that verifies participation in a research study, results from POC testing and confirmation of PrEP eligibility, and a tailored list of area PrEP providers from the AIDSVu PrEP Locator, based on insurance status, location, and scheduling preferences [46]. We will pre-screen the PrEP locator output to ensure that clinics are open to care and accepting new patients, but will not provide PrEP navigation. In contrast to treatment as usual (wherein few WICL can access PrEP), this arm involves an individualized decision aid and onsite POC HIV testing with confirmation of PrEP eligibility in addition to personalized referral services.

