#### Follow-up

Following the baseline interview, participants will be followed with study interviews at months 1, 3, and 6, according to the participant timeline (Fig. 1). Participants will receive a text message or phone call reminder of appointments two days prior to each interview, and researchers will make up to 3 attempts to reschedule missed appointments before marking as “lost to follow up.”

Participants who become incarcerated during the 6-month observation period will continue to be followed and can complete study interviews in-person while in jail or prison, or on return to the community. Participants on PrEP or MOUD may still receive clinical care and follow-up during the incarceration period, though it depends on the discretion of the prison or jail-based clinical providers. All procedures will be approved by the relevant review boards at each CL site prior to study activities, and research staff will obtain necessary approvals to enter CL facilities. Participants who complete study interviews during incarceration may retrieve participation compensation upon release, per CL site regulations. Participants incarcerated > 6 months will be disenrolled and invited to re-enroll if they meet eligibility requirements upon their return to communities. We will re-consent them upon their return to communities to ensure they do not experience real or perceived coercion.

For participants in either arm who receive PrEP and/or MOUD during the study, the prescribing clinician (including the prescribing clinician for Athena participants if applicable) will be responsible for monitoring and managing potential side effects of PrEP and/or MOUD. To minimize missed appointments, clinicians will assess any possible barriers to completing the appointment (i.e., transportation or connectivity issues) and send a reminder call or text message the day before the appointment. Alternatively, participants may request to schedule their follow-up clinician visit on the same day as their follow-up interview for convenience. If participants are identified as having a new health condition (for example, a new diagnosis of an STI, pregnancy, HIV, or viral hepatitis), we will adhere to institutional and treatment guidelines and provide referrals for treatment and care. Participants testing positive for HIV or pregnancy on follow-up will be excluded from further study participation and referred to appropriate services.

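### PrEP starts outside the study health systems are sought only on interview days, so detection of the primary outcome is linked to arm and may favour Athena

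*Protocol article*

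**What the plan says.** All of this is in the protocol article.

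- **Endpoint (Measures).** The definition is the same for both arms: "the primary outcome of the study is PrEP initiation, which we measure by pharmacy fill date (record review) with a signed release of information".
- **Care inside the study health systems (Measures).** "We will review the EHR medication list for PrEP and/or MOUD prescriptions after each clinical visit".
- **Care outside them (Measures).** A research assistant obtains fill and refill dates from clinics and pharmacies, "with a signed release of information and a phone call on each follow-up interview day".
- **Athena (Intervention arm).** Visits run through the site record: "the participant will check-in using the dedicated electronic health record (EHR) at each site via mobile app or website". The prescription goes to a pharmacy that the participant chooses, and "The patient will then be responsible for obtaining the medication from the pharmacy".
- **Control (Enhanced standard of care arm).** Women receive "a tailored list of area PrEP providers from the AIDSVu PrEP Locator". The study checks that listed clinics are taking new patients "but will not provide PrEP navigation".
- **Interviews (Follow-up).** They fall at months 1, 3 and 6. If one is missed, "researchers will make up to 3 attempts to reschedule missed appointments before marking as" lost to follow-up.

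**The concern.** The two capture routes are defined by where care is given, but randomisation largely decides where care is given. An Athena prescription appears in the site EHR whether or not the woman comes to interviews, so staff know that there is a fill to look for. A control woman who starts PrEP with an area provider outside those systems is found through a call that the text ties to an interview day. If she misses interviews, her fill may never be sought.

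A start that is not found and is recorded as no initiation is a misclassified outcome. Intention-to-treat analysis keeps the woman in her arm with the wrong result. Multiple imputation, which the Sample size section offers for missing data, acts only on values recognised as missing. If more starts are missed in control than in Athena, the estimated effect moves in one direction, toward Athena. At stake is whether a difference in initiation can be read as an effect of the strategy or is partly an effect of how starts were found.

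**Working it through.** **1. The plan's own figure.** Inputs from Sample size: 20% versus 40%, 90% power, 106 per arm, 15% attrition, 250 enrolled. Alpha is not stated; two-sided 5% is assumed.

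n per arm = (1.960 + 1.282)² × (0.20×0.80 + 0.40×0.60) / 0.20² = 10.507 × 0.40 / 0.04 = 105.1, so 106.

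212 / 0.85 = 249.4, so 250.

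The sample size reproduces, and no stated figure is wrong.

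**2. Model for unequal capture.** Observed rate = true rate × share of fills captured, with uncaptured fills counted as no initiation. The documents give no capture rate, so every share below is an assumption. The top loss of 15% borrows the planned attrition as an illustration.

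**3. No true effect.** Both arms are truly 20% (the plan's null), with 125 per arm and full capture in Athena. Rejection is by exact binomial enumeration of the pooled chi-square test (the comparison named under Primary analyses), two-sided 5%.

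| Control fills missed | Observed control | Observed Athena | Two-sided rejection |
|---|---|---|---|
| 0% | 20% | 20% | 4.9% |
| 5% | 0.20 × 0.95 = 19% | 20% | 5.3% |
| 10% | 0.20 × 0.90 = 18% | 20% | 6.7% |
| 15% | 0.20 × 0.85 = 17% | 20% | 9.1% |

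The excess lies on the Athena side. At 15% missed, 8.6 of the 9.1 percentage points are rejections in favour of Athena, against 2.4 of 4.9 with equal capture.

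**4. Imperfect capture in both arms.** With 95% in Athena and 85% in control, the observed rates are 0.20 × 0.95 = 19% and 0.20 × 0.85 = 17%, and rejection is about 6.7%. With 85% in both arms it returns to about 4.8%. The gap between arms does the harm.

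**5. Planned effect true (20% versus 40%).**

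| Control capture | Athena capture | Observed rates | Difference |
|---|---|---|---|
| 95% | 100% | 19% vs 40% | 21 points |
| 90% | 100% | 18% vs 40% | 22 points |
| 85% | 100% | 17% vs 40% | 23 points |
| 85% | 95% | 17% vs 38% | 21 points |

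**The case against.** Several points on the other side have force.

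- **Unfilled Athena prescriptions.** A reader might infer that an entry on the EHR medication list is counted as an initiation, which would inflate the Athena rate. The documents do not support this. Measures defines initiation by pharmacy fill date without distinction by arm, and nowhere says that a listed prescription is enough. What stands is narrower: the article spells out how fill dates are obtained only for outside prescriptions.
- **No check after loss to follow-up.** A reader might also infer that a woman marked lost is never checked again. The text does not say so. The call is scheduled for interview days, but her attendance is not stated as a condition, and the release is signed at enrolment (Eligibility criteria). The text is open on this, which is why the point is that fills may be missed, not that they will be.
- **Full Athena capture is generous.** Athena fills also have to be confirmed at a pharmacy of the woman's choice. Seeing the prescription tells staff to look but does not establish the fill. This stands, and step 4 shows the smaller result.
- **15% is near the upper end.** Calls at months 1 and 3 precede many losses, and a completed month-6 call returns earlier dated fills. Women who fill PrEP may be lost less often than others. Some control women may use a provider on the study EHR, and some Athena women may go elsewhere. All of this stands.
- **Coding of missing outcomes.** Nothing says that lost women are counted as non-initiators, and an analysis plan may settle it. That would help with women recognised as missing, but not with an outside fill that nobody knew to seek.
- **A condensed article.** The Supplementary Table and the timeline figure are not shown. Still, the capture procedure is stated in the text, and as stated it differs by place of care.

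**Conclusion.** The point holds. As written, detection of the primary outcome follows place of care, place of care largely follows arm, and the likely direction of any under-detection favours Athena.

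The size is unknown. Under the assumed range at the plan's 20% null, two-sided rejection goes from about 4.9% to between 5.3% and 9.1%, and a true 20-point difference reads as 21 to 23 points. The upper end needs complete Athena capture, a 15% net loss of control fills, and uncaptured fills coded as no initiation. With 95% against 85% capture, rejection is about 6.7%.

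A reader might take the 9.1% as the trial's actual false-positive rate, or regard the primary result as unusable. Neither follows, because the documents permit a capture gap but do not show one. The distortion is modest beside the planned 20-point effect and matters most if the true effect is small. Severity: should fix.

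**What to change.** At the end of the six-month window, run the same check of pharmacy and clinic fill records, under the signed release, for every randomised woman in both arms, whether or not she attended interviews. State that the existing fill-date definition is verified in the same way for in-system and outside prescriptions. State that a missed interview, or being marked lost to follow-up for interviews, does not end record review for the primary outcome.

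The cost is some research-assistant time, a short paragraph of procedure, and possibly a small edit to the release form if it does not cover pharmacies and clinics broadly enough. It is best done while the trial is running, because fills that were never sought may be hard to recover after close-out.

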Those who meet all inclusion criteria will be informed about the study, offered enrollment, and meet with our trained research assistant either onsite immediately or at a scheduled appointment convenient for the participant. At this visit, participants will be formally enrolled by signing a compound authorization/consent to participate (that includes a specific informed consent for telehealth, focus groups, and PrEP if eligible) and a release of information from specified sources for medical, psychiatric, social, and CL system data. Electronic consenting will be done using REDCap. Participants will be sent a PDF of the IRB-approved Compound Authorization Form to their preferred email or text to follow along with the interviewer as the information is displayed on the computer screen. We will perform teach-back techniques to ensure clarity of the informed consent. Participants will indicate consent with a digital signature. Interviewers will also electronically sign a copy of the consent form indicating that all information has been reviewed and understood by the participant. REDCap will save a time-stamped copy of both signed consent forms; the participant will also be offered a copy of the consent form.

Key stakeholders will also be invited to participate in the study. Inclusion criteria for stakeholders are: (1) adults ≥ 18 years old; (2) serve on the community advisory board at either site. Exclusion criteria for this group are: (1) unable or unwilling to provide informed consent; or (2) not comfortable conversing in English.

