## Statistical analyses

### Sample size

The study is powered on the primary outcome, PrEP initiation. The null hypothesis (H0) is that the proportion of participants initiating PrEP in the Athena arm will be the same as in the decision aid-only arm, whereas the alternative hypothesis (H1) is that the proportion of participants initiating PrEP in the Athena arm will be higher than those in the decision aid-only arm. Based on our clinical trial of a decision aid [33], we anticipate ~ 20% of decision aid-only participants will achieve the primary outcome. Based on our demonstration project of eHealth for PrEP for WICL [36], we anticipate 40–50% of Athena participants will achieve the primary outcome. A total sample size of 212 (106 in each group) would achieve 90% power to detect a 20% absolute difference between the two arms. The proportion in the Athena arm is assumed to be 20% under the null hypothesis and 40% under the alternative hypothesis. The proportion in the decision aid-only arm is < 30%. We will inflate the sample size by 15% to account for attrition and will plan to enroll 250 participants total across 2 sites, which is highly feasible. Though we attempt to minimize missing data by having an objectively measured outcome, we have considered additional plans for missing data that include performing both intention-to-treat and per protocol analyses and performing multiple imputation sensitivity analyses if appropriate.

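### The search for PrEP fills outside the study health systems is tied to interview days, so missed interviews may hide more initiations in the control arm than in the Athena arm

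*Protocol article*

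**What the plan says.** All references are to the protocol article.

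- **Outcome.** Measures states that "the primary outcome of the study is PrEP initiation, which we measure by pharmacy fill date (record review) with a signed release of information".
- **Inside the study health systems.** Measures: "We will review the EHR medication list for PrEP and/or MOUD prescriptions after each clinical visit". This step follows clinical visits, not study interviews.
- **Outside them.** Measures has the research assistant obtain "prescription fill and refill dates from clinics and pharmacies with a signed release of information and a phone call on each follow-up interview day". The article describes no other search for outside fills.
- **Route to PrEP, Athena.** Under Intervention arm, care is documented in the site EHR and, where PrEP is indicated and wanted, "the clinician will electronically prescribe PrEP to the patient’s choice of pharmacy". Collecting the medication is left to the woman.
- **Route to PrEP, control.** Under Enhanced standard of care arm, women receive "a tailored list of area PrEP providers from the AIDSVu PrEP Locator, based on insurance status, location, and scheduling preferences", without navigation.
- **Interviews.** Follow-up sets them at months 1, 3 and 6. After up to three attempts to reschedule, a woman is marked lost.
- **Release.** Eligibility criteria has women sign, at enrolment, "a release of information from specified sources for medical, psychiatric, social, and CL system data".
- **Missing data.** Sample size allows 15% attrition and continues "Though we attempt to minimize missing data by having an objectively measured outcome". It then names intention-to-treat and per-protocol analyses, with multiple imputation as a sensitivity analysis if appropriate.

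**The concern.** The trigger for finding the primary event depends on where the woman obtains care, and where she obtains care depends on her arm by design. Athena prescriptions arise in an EHR that is checked without regard to interviews. Many control prescriptions will arise elsewhere, where the stated search takes place on interview days.

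A fill made before a later completed interview can still be found at that interview. The women at risk of being misread are those who fill after their last completed interview. If such a woman is then scored as not having initiated, control events are under-counted more than Athena events. The expected direction favours the intervention in an unblinded trial. An objective endpoint does not protect against this, because the problem lies in whether the record is looked for.

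**Working it through.** **1. The plan's own figure.** The inputs from Sample size are 20% v 40% and 90% power. The article states no significance level, so two-sided 5% is assumed. With the unpooled normal approximation, the number per arm is

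(1.960 + 1.282)² × (0.20×0.80 + 0.40×0.60) / 0.20² = 105.07, so 106 per arm and 212 in total.

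For attrition, 212 / 0.85 = 249.4, so 250. Both figures reproduce. The point concerns how events are found, not the sample size.

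**2. Model for undetected events.** Let L be the share of initiators with no interview-day search after their fill. Let u (control) and v (Athena) be the shares of fills that only such a search would find. If unsearched women count as non-initiators, then

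observed rate = true rate × (1 − L × share outside).

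L = 15% borrows the plan's attrition allowance. L, u and v are assumptions, because the article gives none of them.

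**3. No true effect, both true rates 20%, 125 per arm.** The last column is the probability that the pooled two-proportion z statistic exceeds 1.96 in Athena's favour, by exact binomial enumeration.

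| L | u, v | Control observed | Athena observed | Spurious difference | P(significant for Athena) |
|---|---|---|---|---|---|
| 0 | any | 20.0% | 20.0% | 0 | 2.4% |
| 15% | 80%, 30% | 0.20×(1−0.12) = 17.6% | 0.20×(1−0.045) = 19.1% | +1.5 points | 4.8% |
| 15% | 100%, 0% | 0.20×0.85 = 17.0% | 20.0% | +3.0 points | 8.6% |
| 15% | 100%, 100% | 17.0% | 17.0% | 0 | 2.4% |
| 30% | 80%, 30% | 0.20×(1−0.24) = 15.2% | 0.20×(1−0.09) = 18.2% | +3.0 points | 9.0% |

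**4. Design effect true (20% v 40%), L = 15%.**

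- u = 80%, v = 30%: 38.2% − 17.6% = 20.6 points.
- u = 100%, v = 0%: 40% − 17% = 23 points.
- u = v = 100%: 34% − 17% = 17 points.

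The direction therefore depends on the asymmetry. If both arms relied equally on the calls, there would be no shift under the null, and a true effect would be diluted, not inflated.

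**The case against.** Several stronger readings are tempting, and the text does not carry them.

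- **That Athena events cannot be lost.** The outcome is a fill, but the EHR list shows prescriptions, and Athena women fill at a pharmacy of their choosing. Some may also obtain PrEP elsewhere, and control women may use a provider inside the EHR-covered systems. The asymmetry is one of degree.
- **That a woman who misses interviews is never searched.** The interview-day clause gives the timing of the call. It does not say that the call is dropped when she fails to attend. The release is signed at enrolment and the information comes from clinics and pharmacies, so her presence is not strictly needed. Interviews can be rescheduled, and they can be completed during or after incarceration.
- **That unsearched women are scored as non-initiators, leaving imputation nothing to act on.** No section states this rule. Inflating enrolment for attrition and mentioning imputation fit a missing classification at least as well.
- **That same-day booking favours Athena attendance.** Follow-up does say that "participants may request to schedule their follow-up clinician visit on the same day as their follow-up interview for convenience". However, that paragraph opens by referring to participants in either arm, and the option is not clearly confined to Athena.

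Two further points have force. Attrition of 15% of women need not mean 15% of events, since fills already found at month 1 or 3 stay counted. The article is also a condensed account, and the supplementary outcome table is not shown, so tracing details may be set out elsewhere.

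What remains is what the article does fix: the one search it describes for outside fills is scheduled by interview day, the in-system review is not, and source of care follows arm.

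**Conclusion.** The point holds as a possible bias of modest size. Followed as written, the rule makes detection of the primary event depend more on interview attendance in the control arm than in Athena. At the planned 15% attrition and equal true rates of 20%, the artefact is about 1.5 points under the 80% v 30% split and at most about 3 points in the extreme split. The one-sided error favouring Athena is about 4.8% and 8.6% respectively, against 2.4% without the problem. Even the extreme case is small beside the 20-point design effect.

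These figures require that unsearched women count as non-initiators and that control fills lie outside the EHR more often than Athena fills. A certain, one-sided bias might be inferred, but the article does not establish it. The point still deserves action, because it touches the primary endpoint, its expected direction favours the intervention, and it may be hard to repair after close-out if the signed releases do not cover the pharmacies and prescribers concerned.

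**What to change.** - State that, for every randomised woman in both arms, the same pharmacy, clinic and EHR fill query is run at the end of the 6-month window, whether or not she attended interviews.
- Word the enrolment release so that it permits this query, including at pharmacies and prescribers not named at baseline.
- Classify a woman as a non-initiator only when the query was completed. Otherwise class her outcome as missing, so that the planned imputation can address it.
- Report query completion by arm.

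The cost is a short protocol addition, broader release wording, and some extra research-assistant calls for women who missed interviews.
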